### Research ethics approval

3.13

This study was approved by the Ethics Committee of MUMS and Medical School (IR.MUMS.fm.REC.1396.160, 2017-08-13).

### Confidentiality

3.14

Participants’ personal information will be kept separate from the main dataset and will not be made publicly available. It will be stored on a secure file server research drive at MUMS to ensure confidentiality protection before, during and after the study.

## Results

4

We have complete preliminary qualitative and expert opinion studies that provide educational content, profile information, and intervention design. Recruitment of participants has not been completed and results will be published in 2019. The IVRS is potentially useful to help KT recipients improve self-management outcomes. Using IVRS intervention will make significant differences between BAASIS, SF-12V2, K-TUT scores, when comparing these at baseline and at the end of study.

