Health education programs are aimed to improve outcomes, increase the benefits for the community, and, consequently, enhance public health.^[26]^ More specifically, the program logic model (PLM) helps to identify the measurable outcomes in the causal chain.^[27]^ PLM offers a framework to guide the content of e-health education programs, enabling the healthcare providers to more effectively define and measure objectives, empower patients, and improve patient care.^[28]^ The PLM will be used during the development and implementation phases of this study. According to the PLM, patient education results in proximal outcomes (eg, knowledge and compliance) and intermediate outcomes (eg, self-efficacy and QoL). As a long-term effect, patient education programs might decrease or eliminate the loss of productivity, increase community capacity, and increase the efficiency of health care resources. Since post-transplant management is a complex process and KT recipients have a lot to learn, inadequate patient knowledge can easily result in dire consequences (eg, decreased adherence to recommendations and organ rejection).^[29,30]^ We hypothesized that automatic IVRSs designed based on educational and theory-driven intervention which is acceptable to the individual patient would improve self-management in KT recipients who received IVRS compared to patients who only received usual care. Thus, we designed a randomized, 2 parallel groups controlled trial to evaluate the effect of an IVRS intervention on self-management outcomes (such as immunosuppressant medication adherence, transplant knowledge, and quality of life) among KT recipients.

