### Participants

3.3

KT recipients who will be referred to the center in July 2018 for follow up visits and caretaking are screened for eligibility. Eligible patients will be asked to provide consent with appropriate trail information and enough time to study and ask questions. Patients will be received 2 types of information related to the study:

(1)fully understandable oral information(2)2informed consent, in which the study design is described completely.

Informed consent has already been evaluated by the Ethics Committee of MUMS (IR.MUMS.fm.REC.1396.160). We ensure participants can withdraw from the study at any time without any commitment and no effect on their subsequent care. Eligible participants will be included after completing informed consent.

The inclusion criteria are as follows:

(1)KT recipients who have received a KT between 20 March 2012 and 20 March 2017,(2)having 18 years of age or more,(3)having acceptable graft function (do not need any types of dialysis),(4)having access to a mobile phone,(5)being able to read the informed consent information, and(6)willingness to participate.

The patients who are refused to participate in the study will be excluded. KT patients will be randomly assigned to the control (usual care) or intervention (usual care plus IVRS) groups. Usual care includes an educational booklet for KT and patient education provided by the nephrologists.

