### Outcomes measure

3.5

Study outcomes will be evaluated in accordance with Table 1. Primary and secondary outcomes are measured at baseline, and at 2-months, 4-months, and 6-months after baseline. For ethical reasons, if the intervention is found to be effective, all groups will have access to IVRS at the end of the intervention. Primary outcome will be immunosuppressive medication adherence that is evaluated based on a self-report in both groups during the follow-up period. The secondary outcomes include transplant knowledge, HRQoL, and rehospitalization rate.

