### Statistical analysis

3.12

For participants in the 2 groups, the intervention and control, medication adherence will be measured and documented based on the BASSIS self-report at baseline, 2, 4, and 6 months. For determining effect of each predictor variable and modifying the effect of confounding, we will use ordinary logistics regression and multinomial logistics regression models. To evaluate quantitative variables at different time points, if the variables have a Gaussian distribution, the repeated ANOVA measure, and otherwise the Friedman test, will be used. Cochrane test will be used to evaluate and compare medication adherence across different time points. *P*-values less than .05 will be considered as statistically significant. All statistical analyzes will be performed using the Statistical Package for the Social Sciences, version 23, IBM. The electronic data file is stored on secure data servers and its hard copy version will be stored in a locked file at MUMS.

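### The hypothesis and sample size compare IVRS with usual care, but the expected result and the tests named for adherence and non-Gaussian scores compare time points, so a change shared by both arms could be reported as an IVRS effect

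*Protocol article*

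**What the plan says.** **Question.** The Introduction hypothesises that the IVRS "would improve self-management in KT recipients who received IVRS compared to patients who only received usual care". Section 3.6 bases its 40 patients per group on medication adherence in control versus intervention. Section 3.5 gives the primary outcome: "Primary outcome will be immunosuppressive medication adherence that is evaluated based on a self-report in both groups during the follow-up period".

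**Tests.** Section 3.12 names these analyses:
- Adherence: "Cochrane test will be used to evaluate and compare medication adherence across different time points".
- Scores: "To evaluate quantitative variables at different time points, if the variables have a Gaussian distribution, the repeated ANOVA measure, and otherwise the Friedman test".
- Regression: "For determining effect of each predictor variable and modifying the effect of confounding, we will use ordinary logistics regression and multinomial logistics regression models".

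**Expected result.** Section 4 expects the IVRS to produce significant differences in BAASIS, SF-12V2 and K-TUT scores "when comparing these at baseline and at the end of study". The control group is not mentioned in that sentence.

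**The concern.** A change from baseline within an arm and a difference between randomised arms are different estimands, and they can disagree. The first needs no control group. It adds together any IVRS effect and whatever would have happened anyway. Only the second uses the randomisation to remove the common part.

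Some common change is possible here. Both arms complete the same instruments at baseline and at 2, 4 and 6 months, the primary outcome is self-reported, and section 3.9 accepts that participants cannot be fully blinded. Both arms also have usual care: "Usual care includes an educational booklet for KT and patient education provided by the nephrologists". If a time-point test is taken as the evidence of benefit, any such change is credited to the IVRS, on the primary outcome as well as the scores.

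**Working it through.** **1. The plan's own figure.** Section 3.6 gives 40 per group at 90% power and two-sided α = 0.05, but no rates, SD or effect size, so the 40 cannot be reproduced. Inverting the two-mean formula gives d = (1.960 + 1.282) × √(2/40) = 0.72. For proportions, 40 per group corresponds to about 40% versus 75%. Either way it is a between-arm quantity. Nothing below rests on it.

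**2. What each named test can detect.**
- Cochran's Q (reading the article's spelling as this test), for k visits with column totals C and patient totals R: Q = (k−1)[kΣC² − (ΣC)²] / (kΣR − ΣR²), on k−1 degrees of freedom. Arm does not appear.
- Friedman ranks visits within each patient. Arm does not appear.
- Running either test in each arm separately and comparing the p-values is not a test of the difference between arms.
- Repeated-measures ANOVA and logistic regression can carry arm or arm-by-time terms. Section 3.12 names neither term, and for the regressions it names no outcome or time point.

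**3. Expected values.** Let s be the change shared by both arms and δ the IVRS effect. The expected baseline-to-end change in the IVRS arm is s + δ. The expected difference between arms in that change is (s + δ) − s = δ. With δ = 0 and s > 0, the first is not zero and the second is.

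**4. Size for adherence (δ = 0).** The documents give 60 per arm, four visits and the 0.05 level. Assumed: 40% adherent at baseline, the same even rise in both arms, and latent correlation 0.5 between visits. There were 4,000 simulated trials. The McNemar test is exact and compares baseline with month 6. The between-arm test is z = (p₁ − p₂)/√[p̄(1−p̄)·2/n] at month 6. The table gives the proportion of trials with p < 0.05.

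| Shared rise, 40% to | McNemar, IVRS arm | Cochran, IVRS arm | Cochran, arms pooled | Between arms |
|---|---|---|---|---|
| 40% (no rise) | 3.1% | 4.8% | 4.6% | 5.2% |
| 50% | 19.2% | 18.5% | 35.3% | 5.2% |
| 60% | 68.3% | 64.6% | 93.8% | 5.2% |
| 65% | 88.9% | 85.5% | 99.6% | 4.8% |

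With 40 per arm, McNemar gives 11.7%, 46.2% and 69.2% for the three rises, and the between-arm test stays near 5%.

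**5. Other assumptions.** These start from 50% adherent, with phi between baseline and end of 0.2 to 0.5 and 20,000 replicates. The exact McNemar test in the IVRS arm is significant as follows:
- 60 patients: 16% to 25% for a rise to 60%, and 63% to 85% for a rise to 70%.
- 30 patients: 8% to 10% and 30% to 44%. Thirty is 60 × (1 − 0.5), what would remain if the 50% in section 3.6 is a dropout rate and all of it occurs.

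At 60 per arm, steps 4 and 5 together span 16% to 89% for shared rises of 10 to 25 points.

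**6. Size for a score.** For a shared gain of g SD and baseline-to-end correlation r, the paired t noncentrality is g√n / √[2(1−r)]. With n = 60 and r = 0.5 (assumed):
- g = 0.3: 0.3 × 7.746 / 1 = 2.32, significant in 63% of trials.
- g = 0.5: 0.5 × 7.746 / 1 = 3.87, significant in 97%.

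Using r = 0.72 instead, g = 0.3 gives 0.3 × 7.746 / 0.748 = 3.11, or 86%. That 0.72 is the K-TUT one-week retest value from 25 recipients (section 3.10) and probably overstates a six-month correlation, so 63% is the safer figure.

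**The case against.** The best defence is that section 4 holds one loosely worded expectation, not a decision rule. It could even be read as comparing the arms at each of the two times. The trial is described as randomised with two parallel groups, it is sized between arms, and section 3.12 opens by referring to both groups. Logistic regression suits a binary adherence outcome and is a natural place for arm. Model terms are often left to an SAP, and none is shown here.

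Much of this stands. A reader might infer that the trial has adopted a before-after success criterion and will report shared change as an IVRS effect. The documents do not support that: no claim rule exists beyond the 0.05 threshold, and an arm term is not excluded.

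Nor do they show that a shared change will occur. Eligibility does not select on poor adherence or low knowledge, so regression to the mean at group level does not follow. Patients were transplanted by 20 March 2017 and screened in July 2018, at least 15 months later, and nothing says that usual care starts or changes at baseline.

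The defence does not remove the mismatch. This is more than omitted detail: the article names tests and an expected result, and the Cochran and Friedman tests as named cannot answer the stated hypothesis.

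**Conclusion.** The point holds as an inconsistency to be reconciled. The Introduction and section 3.6 ask a between-arm question. Section 4, and the tests section 3.12 names for adherence and for non-Gaussian scores, address change over time. A shared change could therefore be reported as an IVRS effect; it is not established that it would be.

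At 60 per arm with no IVRS effect, a baseline-to-end test in the IVRS arm is significant in roughly 15% to 90% of trials for shared rises of 10 to 25 points, against about 5% between arms. The baseline rates, rises and correlations are all assumed, and the lower end applies if the shared change is small. The direction follows from step 3 and needs none of those values. Because it touches the primary outcome, it is worth correcting before results are seen.

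**What to change.** In section 3.12, name a between-arm contrast as the sole basis for any claim of benefit:
- **Adherence:** logistic regression with arm as predictor, adjusted for baseline adherence and the transplant-date stratum, at a pre-stated time point such as month 6. Alternatively, use an arm-by-time term over follow-up. Section 3.5 fixes no single time, so the choice must be written down.
- **K-TUT and SF-12V2:** the baseline-adjusted difference between arms.
- Report each with a 95% CI.

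Reword section 4 to state the expected difference between arms. Label the Cochran and Friedman tests and the within-arm changes as descriptive.

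The data are already planned in both arms, and the article says recruitment was not complete. The cost is a written decision on the primary contrast and its time point. The downside is that a favourable within-arm change can no longer be claimed as a positive result.

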## Discussion

5

IVRS has been used in different parts of health care including after hospital discharge to encourage test adherence, medication adherence in patients with asthma and human immunodeficiency virus, heart disease and self-management in back pain and post-stroke.^[37–43]^ IVRSs are used in medication adherence in different conditions with different functions.^[5,41,44–47]^ Previous studies showed that providing information about the health consequences appeared effective in promoting medication adherence. Such information usually includes the advantages of taking medications or the disadvantages of not taking them.^[42,48]^ In this study, we tried to design an intervention based on barriers for immunosuppressant medication adherence. We will evaluate the effect of educational, reminder, and feedback interventions not only in immediate outcomes such as knowledge and medication adherence, but also on intermediate outcomes such as quality of life and follow-up visits.

An important aspect of our study is that it is based on a behavior change theory. Theory-based interventions can make effective changes in behavior.^[6–8]^ The incentives might be used to reduce intentional and unintentional barriers. We hypothesized that feedback with an incentive message might be more effective than other forms of incentives. Thus the RCT will be conducted in KT recipients to evaluate the effects of the IVRS on improvement of patient self-management. In particular, m-health interventions provide tangible incentives in the form of feedback, which have the potential to warn patients about their health conditions. The interactive elements in the IVRS can potentially help providers to realize the patient self-management or measurement of patient-reported outcomes and examine the process of behavioral changes.

One of the limitations of present is that behavioral change observed during any controlled study may not be directly translated into clinical practice. Change in adherence behavior reached over the period of the study may not be maintained after the program ends. Moreover, an automated program may not effectively satisfy the requirements and needs of all groups of patients.

To be able to effectively use the results of the present study in clinical settings, we may need a preliminary evaluation to better target the recipients of such an intervention. As such, for future studies it may be desirable to examine whether new transplant recipients or non-adherent patients respond differently to this type of intervention than those with longer transplant histories or those who have a better record of medication adherence in the past.
